### Serious adverse events (SAEs)

SAEs are recorded using a Serious Adverse Event (SAE) Report Form. Each participant’s medical notes will be systematically checked for SAEs following completion of the final assessment to ensure that all SAEs are recorded. We will also record any SAEs that come to the attention of the research team. An adverse event is defined by the ISO14155:2011 guidelines for medical device trials as serious if it: (A) results in death, (B) is a life-threatening illness or injury, (C) requires hospitalisation or prolongation of existing hospitalisation, (D) results in persistent or significant disability or incapacity, (E) medical or surgical intervention is required to prevent any of the above, (F) leads to fetal distress, fetal death or consists of a congenital anomaly or birth defect or (G) is otherwise considered medically significant by the investigator. Life-threatening in the definition of an SAE refers to an event in which the subject was at risk of death at the time of the event; it does not refer to an event that hypothetically might have caused death if it were more severe. A planned hospitalisation for a pre-existing condition, without a serious deterioration in health, is not considered to be an SAE.

It is relatively common for this patient group to have SAEs, typically psychiatric hospital admissions, physical health hospital admissions and suicide attempts.

The relationship between Feeling Safer or other research procedures and the occurrence of each SAE will be assessed and categorised. The chief investigator will use clinical judgement to make an initial assessment of the relationship. Alternative causes, such as the natural history of the participant’s underlying condition, concomitant therapy, other risk factors, etc, will be considered. The investigator will also consult the current version of the risk analysis report. The chief investigator will make an initial assessment of whether the SAE is potentially related to the device or trial procedures, and the expectedness, and report as necessary to the regulatory authorities within the appropriate timescales (eg, related and unexpected SAEs to the research ethics committee and adverse incidents to the Medicines and Healthcare products Regulatory Agency (MHRA)). The decisions about relatedness and expectedness will be reviewed by the DMEC chair (an independent clinician) in the first instance, and later taken to a DMEC meeting.

We will also record adverse events that are not serious. This would include any adverse device effects from the online programme, including those resulting from insufficient or inadequate instructions for use, deployment, installation or operation, or any malfunction of the software. It also includes any event resulting from user error or intentional misuse.

### Data management

All trial data are entered on paper or electronic clinical research forms (CRFs) and transcribed or entered directly to the clinical data management system. The web-based MACRO Electronic Data Capture (EDC) system is used, programmed and managed by the King’s CTU. Data are pseudonymised using a unique study ID. Personal data and participant identification codes are kept separately from the research data. Access to these data is strictly on a need to know basis. Data are transferred from paper CRFs to the clinical database, or recorded directly on eCRFs as soon as possible after a study visit. Validation of all data entered into the clinical database is achieved through manual review. All critical data items will be 100% checked against original source documents, where applicable, to ensure accuracy, and an error rate is established across all fields to ensure a consistently accurate data set.

### Analysis

A full statistical analysis plan will be approved before any analysis. We will report data in line with the Consolidated Standards of Reporting Trials (CONSORT) 2018 SPI^40^ and 2025 statements^41^ showing attrition rates and loss to follow-up. All outcome analyses will be conducted by statisticians at King’s College London under King’s Clinical Trials Unit standard operating procedures. The target estimand is the treatment policy estimand, and all primary and secondary analyses will be carried out following the intention to treat principle, incorporating data from all randomised participants who provide follow-up data for at least one timepoint, irrespective of intervention received. Every effort will be made to follow up all participants in both arms for research assessments.

Descriptive statistics within each randomised group will be presented for baseline values. These will include counts and percentages for binary and categorical variables, and means and SD or medians with lower and upper quartiles, for continuous variables, along with minimum and maximum values and counts of missing values. There will be no tests of statistical significance or CIs for differences between randomised groups on any baseline variable.

Treatment effects for the primary and secondary outcomes will be estimated using linear mixed models fitted to outcome variables at all follow-up timepoints. Fixed effects will be centre, baseline assessment for the outcome under investigation, treatment, time and time*treatment interactions. Participants will be included as a random intercept to account for repeated measures and Feeling Safer deliverer to account for clustering by Feeling Safer deliverer, treating the control participants as clusters of size 1. Marginal treatment effects will be estimated for the primary outcome (PSYRATS-Delusions) at each time point and reported separately as adjusted mean differences in scores between the groups with 99% CIs and two-sided p-values. For secondary outcomes, the same approach will be followed using linear mixed models to estimate and report the treatment effect at each time point. Cohen’s d effect sizes will be calculated as the adjusted mean difference of the outcome divided by the sample SD of the outcome at baseline. These will be displayed in a forest plot showing the treatment effects on the primary and the secondary outcomes at 6 months. We will also assess minimal response rates, defined as a 20% reduction in PSYRATS-Delusions total score.

We will check for differential predictors of missing outcomes by comparing responders to non-responders on key baseline variables. Any significant predictors will be included in the analysis models in a sensitivity analysis. This accounts for missing outcome data under a missing at random assumption, conditional on the covariates included in the model. As a sensitivity analysis, we will assess whether treatment adherence is associated with missing data, and if it is associated, use inverse probability weights or multiple imputation to compare results.

To test the moderation hypotheses, we will extend the analysis model for the PSYRATS-Delusions to include as fixed effects the putative moderator and its interaction with treatment; the coefficient of the interaction tests whether there is a differential treatment effect across levels of the moderator variable.

To test the mediation hypotheses, we will estimate causal mediation estimands using parametric regression models/structural equation models that are extended for multiarm trials and allow for multiple mediation. All mediation analyses will be adjusted for baseline measures of the mediator, outcomes and possible measured confounders.

A separate Health Economic Analysis Plan will be written in accordance with best practice for economic evaluations alongside a clinical trial. We will conduct a within-trial cost-utility analysis following the intention-to-treat principle and considering two perspectives: (1) NHS and Personal Social Services (NHS&PSS) and (2) societal (incorporating NHS&PSS and wider costs). The primary outcome measure of the economic evaluation will be incremental cost per quality-adjusted life year (QALY). The health-related quality of life instruments EQ-5D-5L and ReQoL-20 collected at baseline, 6 and 9 months will provide the utility values for the calculation of QALYs. We will estimate the costs of providing the Feeling Safer intervention using a micro-costing approach capturing training, travel and therapy delivery time, supervision time, technical support staff, consumables and capital expenditures. An adapted version of the CSRI^34 35^ will be used to collect participant data on use of healthcare (eg, GP attendances, A&E attendances, contacts with mental health teams and admissions to acute hospital) and social care services (eg, social worker, recovery worker), health-related impact on work, contact with criminal justice services and informal care received. Data on admissions to psychiatric hospital and psychotropic medication prescribed will be obtained by reviewing mental health trust medical record notes. These will be valued using national unit costs data sets such as NHS Reference Costs, British National Formulary and published literature, where appropriate. Costs and QALYs will not be discounted given the 12 months horizon. Differences in costs and utilities between arms will be estimated using multilevel mixed-effects linear regression models to allow for multiple follow-ups clustered by participant. Missing data will be imputed following best practice methods, and joint uncertainty around incremental total costs and QALYs will be estimated using seemingly unrelated regression.

The RCT is powered to test whether treatment delivery of Feeling Safer is effective for each staff group compared with TAU (not to test equivalence or non-inferiority between staff groups). We will account for multiple testing of three comparisons (PSW vs TAU; graduate mental health worker vs TAU; CBT therapist vs TAU), so the conservative alpha level is 0.05/3=0.0167. For 90% power, allowing for 10% attrition, we require 121 people per arm to detect an effect size of 0.5 on the PSYRATS total score (ie, a moderate effect size).^42^ The face-to-face Feeling Safe programme produced a large effect size (d=1.2) reduction in PSYRATS total score above that of an alternative (and beneficial) psychological therapy.^9^ The within-group effect of Feeling Safe on PSYRATS total scores was extremely large (d=2.8), which was even higher than in our original proof-of-concept testing (d=2.3).^8^ It is a therapy deliberately designed to produce large effects. Nonetheless, to be conservative, we power the trial of the supported online version (Feeling Safer) to detect a moderate effect (d=0.5), just above that of general CBT for psychosis approaches compared with TAU (d=0.3).^43^ Minimal response is defined in schizophrenia trials as a 20% symptom reduction.^44^ The trial will have 98% power to detect Feeling Safer achieving a minimal response (20% reduction in total PSYRATS score) in 60% of patients compared with 30% in TAU and 90% power to detect Feeling Safer achieving a minimal response in 55% of patients compared with 30% in TAU.

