### Research questions

#### Primary research question

For patients with persistent persecutory delusions in the context of a psychosis diagnosis, can Feeling Safer, when added to treatment as usual (TAU), delivered by either peer-support workers (PSW), graduate mental health workers or cognitive behavioural therapy (CBT) therapists, compared with TAU, reduce persecutory delusions? The primary end-point is 6 months (end of therapy).

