## Methods and analysis

### Trial design and flowchart

The design is a multicentre, single-blind (outcome assessor), parallel, four-arm RCT testing the addition to TAU of Feeling Safer provided by each of three staff delivery groups against TAU. Moderation and mediation tests are built into the trial design. We wish to determine the ‘in toto’ benefits of the programme when added to standard care (ie, the total effect for patients if implemented in the NHS). 484 patients will be randomised to one of the four conditions: Feeling Safer (added to TAU) supported by PSW, or graduate mental health workers including assistant psychologists, or CBT therapists or TAU. Feeling Safer will be provided for 6 months with a staff member. Assessments will be conducted at 0, 3, 6 (end of treatment) and 9 (follow-up) months in person or online by research assistants blind to group allocation. A summary of the trial design can be seen in figure 1. The trial will take place in five centres: Bristol/Darlington/Manchester/Newcastle/Oxford. The NHS trusts will be Avon and Wiltshire Mental Health Partnership NHS Trust; Greater Manchester Mental Health NHS Foundation Trust; Tees, Esk and Wear Valley NHS Trust; Cumbria, Northumberland, Tyne and Wear NHS Foundation Trust; Oxford Health NHS Foundation Trust; Berkshire Healthcare NHS Foundation Trust; Northamptonshire Healthcare NHS Foundation Trust; Central and North West London NHS Foundation Trust (Milton Keynes). The University of Oxford is the trial sponsor. There is a data monitoring and ethics committee (DMEC) and trial steering committee.

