### Randomisation, blinding and code-breaking

Patients will be randomised once they have completed the baseline assessment. Randomisation, using an online system from King’s Clinical Trial Unit (CTU), will use a permuted blocks algorithm, with randomly varying block size, stratified by centre, in a 1:1:1:1 ratio.

The research assessors will be blinded to group allocation, but the patients and allocated staff member will not be (they cannot be blinded to whether a psychological intervention is delivered or not). The Feeling Safer treatment deliverers will inform patients of the randomisation outcome to ensure that the research assessors remain blinded to group allocation. Precautionary strategies to prevent unblinding of allocation include the staff member and assessor considering room use and booking arrangements; patients being reminded by the assessor not to talk about their allocation result; and, after the initial assessment, the assessor not looking at the patient’s clinical notes. If an allocation is revealed between assessment sessions, this is logged by the trial coordinator, and whenever possible, re-blinding will occur using another assessor.

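### The three primary comparisons are to be judged at alpha 0.0167 but shown with 99% CIs, so a significant result can carry an interval that includes zero

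*Protocol article*

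**What the plan says.** Both statements stand in the Analysis section of the protocol article.

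- The sample-size paragraph names the family of tests: "We will account for multiple testing of three comparisons (PSW vs TAU; graduate mental health worker vs TAU; CBT therapist vs TAU". It then gives the level: "so the conservative alpha level is 0.05/3=0.0167". The trial is sized on that level: "For 90% power, allowing for 10% attrition, we require 121 people per arm to detect an effect size of 0.5 on the PSYRATS total score".
- The paragraph on the mixed models gives the reporting format for the primary outcome at each time point: "adjusted mean differences in scores between the groups with 99% CIs and two-sided p-values". It states no significance threshold.

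The primary research question fixes the time point of the decision: "The primary end-point is 6 months (end of therapy".

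The article gives no reason for 99%, does not call the interval descriptive, and mentions no alpha of 0.01. The level 0.0167 is the only test level it states.

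**The concern.** A two-sided CI at level 1 − alpha excludes zero exactly when the matching test has p below alpha. A reader who sees an interval printed beside a p-value for the same estimate will expect the two to agree. Here they need not agree, because 0.0167 corresponds to 98.33% and 99% corresponds to 0.01.

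The trial is designed to give a separate answer for each staff group. If the peer-support comparison, for example, came out at p=0.013, the stated alpha would call it a success while the published interval crossed zero. Different readers could then report different conclusions from one result, and the choice between them would be made after the result was known.

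**Working it through.** **Inputs (protocol article).** Three comparisons, alpha 0.05/3, 90% power, d=0.5, 10% attrition and 121 per arm (Analysis); allocation "stratified by centre, in a 1:1:1:1 ratio" (Randomisation, blinding and code-breaking); 484 in total (Trial design and flowchart). The value d=0.3 is the effect that the sample-size paragraph cites for general CBT for psychosis against TAU. The outcome is standardised to SD 1.

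**1. The plan's own sample size.** n per arm = 2(z₁₋α/₂ + z₀.₉₀)²/d².
- With alpha 0.0167: 2 × (2.394 + 1.282)²/0.25 = 108.1, or 109 after rounding up.
- Allowing for attrition: 108.1/0.9 = 120.1, which rounds up to 121. (Rounding to 109 before dividing gives 122.)
- 4 × 121 = 484. The stated figure is reproduced at alpha 0.0167.
- Analysed per arm: 121 × 0.9 = 108.9, taken as 109.

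**2. The matching interval.**
- 1 − 0.05/3 = 0.9833, critical value 2.394.
- 99% interval: critical value 2.576.
- Ratio of widths: 2.576/2.394 = 1.076.

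**3. Where the two disagree.** The standard error of d is √(2/109) = 0.1355.
- The test is significant when the observed d exceeds 2.394 × 0.1355 = 0.324.
- The 99% CI excludes zero when the observed d exceeds 2.576 × 0.1355 = 0.349.
- Example, observed d=0.335: z = 0.335/0.1355 = 2.47, p≈0.013. The 98.33% CI is 0.335 ± 0.324, or 0.011 to 0.659. The 99% CI is 0.335 ± 0.349, or −0.014 to 0.684.

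**4. How often, per comparison.** P(0.01<p<0.0167) = Φ(d/SE − 2.394) − Φ(d/SE − 2.576); the opposite tail is negligible for d of 0.3 or more.

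| True d | p<0.0167 | 99% CI excludes zero | Disagreement |
|---|---|---|---|
| 0 (both tails) | 1.67% | 1.00% | 0.7% |
| 0.3 | 42.9% | 35.9% | 7.0% |
| 0.4 | 71.2% | 64.7% | 6.5% |
| 0.5 | 90.3% | 86.8% | 3.5% |

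**5. At least one of three.** A simulation of one million trials with a shared TAU arm gives about 10% at d=0.5, 18% at d=0.4 and 19% at d=0.3, taking the same true effect in all three arms. These respect the upper bounds of three times the single-comparison figure: 10.5%, 19.5% and 21.0%.

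**6. Only if the 99% CI were read as the decision criterion.**
- Power at d=0.5 would be about 86–87% (86.8% by the normal approximation, about 86% by the t-test) instead of about 90%.
- Restoring 90% would need 2 × (2.576 + 1.282)²/0.25 = 119.0, rounded up to 120 analysed; 120/0.9 = 133.3, so 134 randomised per arm and 4 × 134 = 536 in total.
- The familywise bound would be 3 × 0.01 = 0.03 instead of 0.05.

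**The case against.** The strongest reply is that the article contains one test, not two. The 99% level belongs to a reporting format. The only threshold is 0.0167, and the p-value that meets or misses it is printed beside the interval. A 99% CI that includes zero next to p=0.013 is not a logical contradiction, since each statement is true at its own level. This stands, and it rules out several stronger readings.

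- A reader might infer that the trial has lost power and needs 134 per arm. The article nowhere makes the 99% CI the criterion, so the planned 90% at alpha 0.0167 is intact.
- A reader might infer a risk of false-positive claims. The reverse holds: a 99% CI that excludes zero always implies p<0.0167.
- A reader might infer that 99% reflects five comparisons, because 0.05/5 = 0.01. The article names no family of five.
- A reader might ask for a separate CI level for secondary outcomes and other time points. The article carries the same approach over to the secondary outcomes, and any further detail can be left to the analysis plan, which is not shown.

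It is also fair to say that the affected window is narrow, an observed d of about 0.324 to 0.349. The article regards d=0.5 as conservative, and at a true d of 0.8 the chance of disagreement is only about 0.02% per comparison.

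What the reply does not remove is the mismatch itself. The article commits to testing at 0.0167 and pairs those tests with an interval at another level, without saying that the interval plays no part in the decision.

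**Conclusion.** The point holds as a mismatch between the stated interval level and the stated test level for the primary comparisons. It is minor to moderate. No estimate, p-value, error rate or sample size is wrong. What is at stake is a clear reading of a primary result with p between 0.01 and 0.0167.

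The probabilities rest on an unadjusted two-sample comparison with 109 analysed per arm and, for the any-of-three figures, equal true effects across arms. The planned model adjusts for baseline and includes a random effect for deliverer. Both would change the standard error, and so the probabilities at a given d, but neither changes the mismatch between 98.33% and 99%.

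**What to change.** In the Analysis section, and in the statistical analysis plan, report 98.33% CIs (1 − 0.05/3) for the three 6-month comparisons of PSYRATS-Delusions with TAU. The interval then excludes zero exactly when p<0.0167.

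If the investigators prefer to keep 99%, one added sentence is enough: the primary decision rests on p<0.0167 for each comparison, and the 99% CI is descriptive.

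Either change costs one line. It needs no new data, does not alter the sample size and has no consequence for participants. It should be made before the analysis plan is approved, so that the reading of a borderline result is fixed before any result is seen.

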### Assessments

The primary outcome is the severity of persecutory delusion assessed by the Psychotic Symptoms Rating Scale (PSYRATS)—Delusions.^14^

Secondary outcomes are as follows: depression (PHQ-9);^15^ anxiety (GAD-7);^16^ insomnia (eight-item Sleep Condition Indicator);^17^ agoraphobia (Oxford Agoraphobic Avoidance Scale);^18^ paranoia (Revised Green *et al* Paranoid Thoughts Scale);^19^ psychological well-being (Warwick-Edinburgh Mental Well-being Scale);^20^ personal recovery (the Questionnaire about the Process of Recovery—15 items);^21 22^ meaningful activity (time budget)^23^ and quality of life (EQ-5D-5L and ReQol-20).^24 25^

The moderators are as follows: age, gender, ethnicity and working memory (WAIS-III digit span forward, digit span backward and letter-number sequencing).^26^

The mediators are as follows: vulnerability and safety beliefs;^9^ negative self-beliefs and positive-other beliefs (Brief Core Schema Scale—negative self and positive others);^27^ positive self-beliefs (Oxford Positive Self Scale Short Form);^28^ worry (Dunn Worry Questionnaire);^29^ insomnia (Sleep Condition Indicator);^17^ defence behaviours (Oxford Paranoia Defence Behaviours Questionnaire),^30^ anomalous experiences (Specific Psychotic Experiences Questionnaire—hallucinations^31^ and Global Felt Sense of Anomaly scale (GFSA))^32^ and social support (Multidimensional Scale of Perceived Social Support).^33^

Service use data will be collected with an adapted version of the Client Service Receipt Inventory (CSRI).^34 35^

For patients in the therapy arms, there will be non-blinded collection by the treatment deliverers of a Modified Client Satisfaction Questionnaire^36 37^ and the theoretical framework of acceptability questionnaire.^38^

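### The stated cost and utility models name clustering by participant only, whereas the clinical model also has a deliverer effect; if deliverers differ, economic standard errors would be too small

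*Protocol article*

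**What the plan says.** All statements are in the protocol article.

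- **Clinical model (Analysis).** Besides the participant intercept there is a random effect for "Feeling Safer deliverer to account for clustering by Feeling Safer deliverer, treating the control participants as clusters of size 1".
- **Secondary outcomes (Analysis).** "For secondary outcomes, the same approach will be followed using linear mixed models". The deliverer term therefore carries over.
- **Secondary outcome list (Assessments).** It includes "quality of life (EQ-5D-5L and ReQol-20"). The health economics paragraph uses the same two instruments to derive utilities.
- **Cost and utility models (Analysis, health economics paragraph).** These are "multilevel mixed-effects linear regression models to allow for multiple follow-ups clustered by participant".
- **Joint uncertainty (same paragraph).** "joint uncertainty around incremental total costs and QALYs will be estimated using seemingly unrelated regression". No clustering is stated for this step.
- **Intervention costing (same paragraph).** Micro-costing "capturing training, travel and therapy delivery time, supervision time, technical support staff, consumables and capital expenditures".
- **Deferral (same paragraph).** "A separate Health Economic Analysis Plan will be written in accordance with best practice". That plan is not available here.

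**The concern.** In the three Feeling Safer arms several patients share a deliverer, so their outcomes may be correlated. The clinical model allows for this. The economic paragraph names a clustering unit, and that unit is the participant, meaning repeated measurements on one person. Seemingly unrelated regression handles the correlation between one participant's costs and QALYs. Without clustered errors it does not handle correlation between different participants of one deliverer.

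The inconsistency is sharpest for EQ-5D-5L and ReQoL-20, which would be analysed with the deliverer level as secondary outcomes and without it as utilities, with no reason given. A deliverer effect on costs is also plausible, since delivery, travel and supervision time are costed and can differ between staff members.

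What is at stake is the precision of the incremental costs and QALYs. Intervals would be too narrow, and the uncertainty about cost-effectiveness would look smaller than it is. The primary clinical analysis is untouched, and nothing here shows bias in the point estimates.

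**Working it through.** **Inputs from the article.** 121 participants per arm; 1:1:1:1 allocation; TAU participants as clusters of size 1.

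**Inputs that are assumptions.** Deliverers per arm, k = 5, 10 or 20; deliverer ICC for total cost or QALYs, ρ = 0, 0.02 or 0.05; all 121 per arm analysed after imputation; equal caseloads; equal total variance in the arms compared.

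**Stated figure first.** The article gives no precision target for the economic analysis, so its sample size is the only figure to reproduce. With "so the conservative alpha level is 0.05/3=0.0167" (two-sided), 90% power and d = 0.5:

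n = 2 × (2.394 + 1.282)² / 0.5² = 108.1, so 109 per arm; 109 / 0.9 = 121.1.

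The stated 121 is reproduced. It serves below only as the arm size.

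**Formulas.** Patients per deliverer: m = 121/k. Design effect in a Feeling Safer arm: DE = 1 + (m − 1)ρ; in TAU it is 1.

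- Factor by which the standard error (SE) should grow, one arm against TAU: f = √[(DE + 1)/2].
- Three arms pooled against TAU: f = √[(DE/3 + 1)/(4/3)] = √[(DE + 3)/4].
- Understatement of the SE when the level is left out: 1 − 1/f.
- True coverage of a nominal 95% interval: 2Φ(1.96/f) − 1.

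**Example.** k = 10, ρ = 0.05: m = 12.1; DE = 1 + 11.1 × 0.05 = 1.555; f = √(2.555/2) = 1.130; understatement = 1 − 1/1.130 = 11.5%; coverage 91.7%.

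| k | m | ρ | DE | f, one arm | SE understated | Coverage | f, pooled | SE understated | Coverage |
|---|---|---|---|---|---|---|---|---|---|
| 5 | 24.2 | 0.02 | 1.464 | 1.110 | 9.9% | 92.3% | 1.056 | 5.3% | 93.6% |
| 5 | 24.2 | 0.05 | 2.160 | 1.257 | 20.4% | 88.1% | 1.136 | 12.0% | 91.6% |
| 10 | 12.1 | 0.02 | 1.222 | 1.054 | 5.1% | 93.7% | 1.027 | 2.7% | 94.4% |
| 10 | 12.1 | 0.05 | 1.555 | 1.130 | 11.5% | 91.7% | 1.067 | 6.3% | 93.4% |
| 20 | 6.05 | 0.02 | 1.101 | 1.025 | 2.4% | 94.4% | 1.013 | 1.2% | 94.7% |
| 20 | 6.05 | 0.05 | 1.253 | 1.061 | 5.8% | 93.5% | 1.031 | 3.0% | 94.3% |

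At ρ = 0 every factor is 1 and nothing is understated.

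The pooled columns matter because the Abstract describes the economic comparison as Feeling Safer against TAU, while the economic paragraph speaks of differences between arms. Either contrast could be meant.

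**The case against.** The strongest reply is that this is one condensed paragraph in a journal article. It says what the multilevel model allows for; it does not say that no other level will be used. The sentence on seemingly unrelated regression is silent about standard errors, so clustered errors or a bootstrap would be compatible with it. The full specification belongs to a separate plan, which may add the deliverer. This stands, and it rules out the reading that the trial has decided to ignore deliverer clustering or that its uncertainty is in fact understated. It does not remove the point: the article goes beyond deferral by naming the clustering unit and the joint method, and what it names differs from the clinical model for the same data.

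A reader might also infer that deliverers determine support time and travel, so that clustering in costs must be at least as strong as in outcomes. The article does not support that. The section on the supported online programme lets the level and type of support follow the patient's need, which is variation between patients. The quantity analysed is total cost, which also includes admissions, medication, social care and, in the societal perspective, wider costs. An ICC argued for delivery cost alone, such as 0.10, cannot be carried over to that total and is not used here. The equal-variance formula would not suit delivery cost either, because TAU participants incur none.

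Finally, every size given rests on assumed ICCs and caseloads, and pooling the arms roughly halves the effect. This also stands.

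**Conclusion.** The point holds in a conditional form. The economic models as stated do not name the deliverer level that the clinical model uses, and EQ-5D-5L and ReQoL-20 fall under both. Followed as written, with a positive deliverer ICC for total costs or QALYs, the economic standard errors would be too small. For an assumed ICC of 0.02 to 0.05 and 5 to 20 deliverers per arm, that is about 2% to 20% for one arm against TAU, with a nominal 95% interval covering about 94% down to 88%. Pooled, it is about 1% to 12%. The article supplies neither ICC nor caseload, so the true size is unknown and could be nil. Severity is minor: the remedy is simple and the trial's own clinical model already supports it.

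**What to change.** State the following in the Health Economic Analysis Plan before any analysis:

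1. The cost and utility models include a random effect for Feeling Safer deliverer, with TAU participants as clusters of size 1, as in the clinical model.
2. The imputation model for missing costs and utilities respects the same level.
3. Joint cost-QALY uncertainty is estimated with deliverer-clustered errors in the seemingly unrelated regression, or with a cluster bootstrap.

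If the deliverer level is to be left out, the plan should give the reason. The cost is wording, a little more analysis work and possibly wider intervals. No change to recruitment, data collection or the clinical analysis is needed, provided the deliverer identifiers used in the clinical model are also available to the economic analysis.
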